## Abstract

**Background:**

Improved organization of trauma care in the acute phase has reduced mortality of trauma patients. However, there has been limited attention for the optimal organization of post-clinical rehabilitation of trauma patients. Therefore we developed a Transmural Trauma Care Model (TTCM). This TTCM consists of four equally important components: 1) intake and follow up consultations by a multidisciplinary team consisting of trauma surgeon and hospital based trauma physical therapist, 2) coordination and individual goal setting for each patient by this team, 3) primary care physical therapy by specialized physical therapists organized in a network and 4) E-health support for transmural communication and treatment according to protocols. The aim of the current study is to assess the cost-effectiveness of the TTCM.

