**Methods:**

Patients will be recruited from the outpatient clinic for trauma patients of the VU University Medical Center (VUmc) if they have at least one fracture and were discharged home. A *controlled-before-and-after* study design will be used to compare the TTCM with regular care. Measurements will take place after the first outpatient clinical visit and after 3, 6 and 9 months. Prior to the implementation of the TTCM, 200 patients (50 patients per time point) will be included in the control group. After implementation 100 patients will be included in the intervention group and prospectively followed. Between-group comparisons will be made separately for each time point. In addition, the recovery pattern of patients in the intervention group will be studied using longitudinal data analysis methods. Effectiveness will be evaluated in terms of health-related quality of life (HR-QOL), pain, functional status, patient satisfaction, and perceived recovery. Cost-effectiveness will be assessed from a societal perspective, meaning that all costs related to the TTCM will be taken into account including intervention, health care, absenteeism, presenteeism and unpaid productivity. Additionally, a process evaluation will be performed to explore the extent to which the TTCM was implemented as intended, and to identify possible facilitators and barriers associated with its implementation.

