## Methods

### Design

To answer the research questions, a modified *controlled-before-and-after* study will be conducted at the outpatient clinic for trauma patients of the VU University Medical Center (VUmc), Amsterdam, the Netherlands. The modification of the original study design -in which both control group and intervention group are observed prospectively- is that in our design only the intervention group will be prospectively followed. This modification is required due to the limited resources available. Prior to the implementation of the TTCM, data of 200 control patients who received care as usual will be collected during an inclusion period of 4 months. The control group will consist of 4 clusters of patients who either had their first consultation at the outpatient clinic for trauma patients of the VUmc 0 (i.e. baseline), 3, 6 or 9 months ago. Per cluster, we aim to include approximately 50 patients, all of whom will be asked to fill out an online questionnaire once after providing informed consent. After implementing the TTCM, patients who enter the outpatient clinic for trauma patients of the VUmc and meet the inclusion criteria will be asked to participate in the intervention group of the study. Patients in the intervention group will be prospectively followed for 9 months (*n* = 100) and will be asked to fill out online questionnaires at baseline, 3, 6 and 9 months after their first consultation at the outpatient clinic for trauma patients. See Fig. 1 for a detailed illustration of the study design.

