### Recruitment

#### Control group

Control group patients will be identified from hospital records. All eligible patients will be contacted by phone by one of the investigators. At this point, patients receive further information about the study, and in- and exclusion criteria will be verified by the coordinating investigator. Patients who are willing to participate and eligible will then receive an email containing a link to an online questionnaire. Clicking the link to the online questionnaire will serve as informed consent. Patients who do not respond within 1 week will receive a reminder email which will be resent after another week of not responding. If the patient does not reply to both emails one of the coordinating investigators will contact the patient by phone to inquire whether the patient is still interested and willing to participate as indicated earlier.

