#### Intervention group

Intervention group patients will be identified during their first consultation at the outpatient clinic for trauma patients. During this consultation, patients will be informed about the study purpose and procedures by one of the investigators. Also, in- and exclusion criteria will be verified. Patients who are willing to participate and are eligible will receive an email containing a link to an online questionnaire. Clicking the link to the online questionnaire will serve as informed consent. Subsequently, patients will be prospectively followed and will receive additional online questionnaires at 3, 6 and 9 months follow-up. Patients who do not respond within 1 week to one of the aforementioned online questionnaires will receive a reminder email which will be resent after another week of non-responding. If the patient does not reply to both emails one of the coordinating investigators will contact the patient by phone to inquire whether the patient is still interested and willing to participate.

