#### Clinical effectiveness

The clinical effectiveness analyses will consist of two parts. First, the TTCMs’ effectiveness in terms of HR-QOL, pain, perceived recovery, functional status and patient satisfaction compared with usual care will be explored at 3, 6 and 9 months follow-up using regression analyses. The four clusters of control patients (i.e. time after their first consultation at the outpatient clinic for trauma patients respectively 0, 3, 6 and 9 months) will be compared with the patients in the intervention group at the corresponding time points. Second, the recovery pattern of patients in of the intervention group will be studied using longitudinal data analysis in terms of HR-QOL, pain, perceived recovery, functional status and patient satisfaction during the 9 month follow-up period (and while receiving the TTCM). All of the aforementioned analyses will be corrected for confounders if necessary (e.g. age, gender, level of education). Confounding will be checked by adding the potential confounding variable to the crude models, and will subsequently be considered to be present if the regression coefficient changes by 10% or more. All of the clinical effectiveness analyses will be performed in SPSS, using a level of significance of *p* < 0.05.

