#### Economic evaluation

The economic evaluation will be performed from the societal perspective, meaning that all costs and consequences related to the intervention will be taken into account, irrespective of who pays or benefits. The mean difference in total costs between the intervention and control group will be compared to the corresponding mean difference in effects. For this, cost and effect differences will be estimated using seemingly unrelated regression analyses in order to correct for their possible correlation. To deal with the highly skewed nature of cost data, 95%CIs around the differences in costs will be estimated using the Bias Corrected and Accelerated Bootstrap method, with 5000 replications. Incremental Cost Effectiveness Ratios (ICERs) will be calculated by dividing the differences in costs by those in effects. To graphically illustrate the uncertainty surrounding the ICERs, bootstrapped incremental cost-effect pairs will be plotted on cost-effectiveness planes [47]. A summary measure of the joint uncertainty of costs and effects will be presented using cost-effectiveness acceptability curves, indicating the probability of an intervention being cost-effective in comparison with the control condition for a range of willingness-to-pay values (i.e. the maximum amount of money decision-makers are willing to pay per unit of effect gained) [48]. To test the robustness of the results, various sensitivity analyses will be performed [49]. All of the economic evaluation analyses will be performed in STATA, using a level of significance of *p* < 0.05.

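### Confounder correction is stated for the clinical analyses only; followed as written, the economic comparison of these non-randomised groups has no case-mix adjustment

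*Protocol article*

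**What the plan says.** The abstract puts the economic question first: "The aim of the current study is to assess the cost-effectiveness of the TTCM".

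Under Design, the comparison is a modified controlled-before-and-after study: "in our design only the intervention group will be prospectively followed". Controls form four separate groups (0, 3, 6 and 9 months after first consultation): "Per cluster, we aim to include approximately 50 patients". For the other arm, "After implementation 100 patients will be included in the intervention group and prospectively followed". The recruitment routes differ. Under Control group: "Control group patients will be identified from hospital records", followed by telephone contact. Under Intervention group: "Intervention group patients will be identified during their first consultation at the outpatient clinic for trauma patients".

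Clinical effectiveness describes two analyses, the between-group regressions and the longitudinal recovery pattern in the intervention group. It then says: "All of the aforementioned analyses will be corrected for confounders if necessary (e.g. age, gender, level of education" (the bracketed examples end there). A covariate counts as a confounder if adding it moves the coefficient by 10% or more.

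Economic evaluation is the next section. It sets the mean cost difference against the mean effect difference and says: "For this, cost and effect differences will be estimated using seemingly unrelated regression analyses in order to correct for their possible correlation". It then describes bias-corrected and accelerated bootstrap intervals with 5000 replications, ICERs, planes, acceptability curves and unspecified sensitivity analyses. It lists no covariates and does not mention the confounder rule.

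**The concern.** In a randomised trial, a cost-effectiveness regression with treatment group as the only regressor would be defensible. Here the groups differ in calendar period and in how patients were found and approached, and the Discussion concedes possible selection bias. Injury type, injury severity and operative treatment can plausibly affect both cost and utility, and any of them may differ between the groups.

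The article does address confounding, but its rule covers one of its two between-group evaluations and leaves out the one named as the study's aim. EQ-5D is the primary outcome and also the source of the QALYs. The same instrument could therefore give an adjusted effect in the clinical results and an unadjusted one in the ICER. The bootstrap describes sampling uncertainty around whatever contrast is fitted, so it would not reveal or remove systematic case-mix differences.

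**Working it through.** The plan states no figure to reproduce. The check is of the text, plus what the stated model does.

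**1. Scope of the rule.** The rule points backwards, to analyses already described. At that point these are the two clinical parts. The economic analyses come afterwards, and each section closes with its own software statement (SPSS for the clinical analyses, STATA for the economic ones), so they read as separate plans.

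**2. Any other source of adjustment.** Descriptive statistics only tabulates baseline characteristics. Handling missing data puts predictors into the imputation model, which is not adjustment of the group contrast. Economic evaluation does not refer back.

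**3. What the stated regression returns.** With the same regressors in both equations, seemingly unrelated regression gives the same point estimates as ordinary least squares run on each equation. If group is the only regressor, each group coefficient is the raw difference in means. The joint model describes how the cost and effect estimates vary together; it does not change what is compared.

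**4. How a case-mix gap enters.** Let a covariate differ by *d* between groups, with effects *b_C* on cost and *b_E* on utility or QALYs. Without adjustment:

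- cost difference = TTCM effect on cost + *b_C* × *d*
- effect difference = TTCM effect on outcome + *b_E* × *d*
- ICER = (first line) / (second line)

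The article gives none of *d*, *b_C* and *b_E*, nor a cost SD, so the bias in the ICER cannot be computed.

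**5. Precision of the balance between groups, for scale only.** The standard error of a standardised covariate difference is sqrt(1/n1 + 1/n2).

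- 100 intervention patients against one control cluster of 50: sqrt(1/100 + 1/50) = 0.173; 1.96 × 0.173 = 0.34 SD
- 100 against all 200 controls: sqrt(1/100 + 1/200) = 0.122; 1.96 × 0.122 = 0.24 SD

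Gaps of this size could arise by chance before any systematic selection. Chance gaps are part of what the bootstrap interval reflects, so these figures do not show bias. They show that groups of this size cannot be relied on to be closely balanced. Systematic selection would add to them and would not be reflected in the interval.

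**The case against.** The strongest reply is that silence is not a statement. The economic section never calls the analysis crude or unadjusted. A mean difference can be an adjusted coefficient, and seemingly unrelated regression accepts covariates. Indeed, with group as the only regressor it adds little to bootstrapping patients' cost-effect pairs, so its choice fits planned covariates at least as well as none. This is a condensed article, and a covariate list is commonly left to the full protocol or analysis plan. All of this stands, and it limits the point to the plan as written. It does not dispose of it: the article chose to state a confounder rule, restricted its scope, and gave the economic regression a different purpose.

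The clinical EQ-5D effect is also adjusted only if the 10% rule calls for it. So the two results *may* differ in adjustment; it is not certain that they will.

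Both groups come from one clinic under the same eligibility criteria, pre- and in-hospital care is said to be unchanged, and the article claims only a first indication of cost-effectiveness. These facts reduce the likely imbalance and the weight of the claim, but they do not remove differences from period and recruitment route.

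A reader might infer a size in euros from the Background's EUR 66,000 per operatively treated vertebral fracture. The document does not support that. The figure comes from a cited study, no time horizon is given, EUR 47,000 of it is absenteeism, and the article gives neither a cost for other patients nor a difference in the share of such injuries. Any simulated bias would likewise only return the confounding put into it.

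**Conclusion.** The point holds in a limited form. The article confines confounder correction to the clinical analyses and states none for the economic evaluation, whose regression is there for cost-effect correlation alone. Followed literally, the cost difference, effect difference, ICER, plane and acceptability curve would compare non-randomised groups without case-mix adjustment.

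This rests on two conditions: that no unseen plan adds covariates to the economic model, and that the groups differ on factors that affect cost or utility. The second is plausible from the design but not shown. The direction and size of any bias cannot be determined from the document. A reader might infer that the trial has committed itself to an unadjusted economic analysis; the text does not go that far. If covariates are already planned, one sentence settles the matter. Because cost-effectiveness is the stated aim and the remedy is cheap, the correction should be made before the economic data are analysed.

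**What to change.** State under Economic evaluation that both the cost and the effect equation include a prespecified set of baseline covariates, refitted in each bootstrap resample and each imputed data set. Candidates already listed under Baseline characteristics for both groups are age, gender, education, medical history, injury type, operative or conservative treatment, and ISS. Base the ICER, plane and acceptability curve on the adjusted differences, and show the crude result as a sensitivity analysis. The set must be named there: the clinical section fixes no covariates to copy, and its examples omit injury type, treatment and severity.

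**Cost.** No new data, and slightly more analysis work. With age and ISS linear and the categories as listed, the set uses 1 + 1 + 2 + 2 + 3 + 1 + 1 = 11 parameters. For 100 intervention patients against one cluster of 50, that leaves 150 − 2 − 11 = 137 residual degrees of freedom. This is affordable, but with only about 50 controls per cluster it is a reason to keep the list short, the more so as ISS forms part of the multi-trauma definition.

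**What this does not fix.** Each control completes one questionnaire, whereas QALYs are to be interpolated between measurement points. Covariates do not supply patient-level QALYs for controls, so how these are obtained needs its own clarification.

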#### Process evaluation

Using Nvivo, data derived from the focus groups will be analyzed in accordance to the constant comparative approach. That is, analytic categories will be inductively established by constantly comparing and checking items with the rest of the data [50]. By starting with open coding, descriptive themes and subthemes will be generated by one researcher. The final codes will subsequently be developed through discussion between two independent researchers. During these discussions, similar codes will be grouped into analytical categories and the different properties of these categories will be explored as well as the relationships between them (i.e. selective coding) [51]. Using SPSS, summary statistics will be prepared to evaluate the new care model’s reach, dose delivered, dose received, and fidelity.

## Discussion

Traumatic fractures are common and pose a substantial economic burden to society. Nonetheless, little is currently known about how to optimally organize the post-clinical rehabilitation process for trauma patients transferred from hospital to primary care. Therefore, the TTCM for the post-clinical rehabilitation of trauma patients was developed at the VUmc, which aims to improve HR-QOL, functional outcome and patient satisfaction of trauma patients, by organizing the post-clinical rehabilitation in an innovative and more efficient way. Within the available resources, the aforementioned *modified controlled before and after design* was regarded as the most optimal research design at this stage. The study aims to provide insight into the new care models’ cost-effectiveness and aims to provide clues as to how to further optimize the TTCM so it is “ready-to-implement” in other hospitals, which can possibly serve as a starting point for a future pragmatic (multicenter) controlled randomized trial. We are of the opinion that even though the applied *modified controlled before and after* design might bear on the internal validity of the current study findings (e.g. due to selection bias), it does not negate the value of its results. Another possible limitation of the proposed study might be the difficulty to identify what components of the TTCM will be responsible for (positive) effects. To illustrate, better clinical outcome could be the result of better educated physical therapists in primary care, but could also be due to the introduction of multidisciplinary consultations at the outpatient clinic for trauma patients. In the current study, a pragmatic design will be applied, in which the TTCM is evaluated as whole. Future research will therefore be needed to provide insight into which TTCM component is accountable for which specific effect.

Despite the shortcomings of the study we aim to provide insight in organizing the post-clinical rehabilitation process for trauma patients in a more efficient way and consequently contribute to better clinical outcomes and reduced societal costs.

## Abbreviations

ATLS®: Advanced trauma life support
DALY: Disability-adjusted life years
GARS: Groningen activity restriction scale
GPE: Global perceived effect
HR-QOL: Health-related quality of life
ICER: Incremental cost effectiveness ratios
ISS: Injury severity score
LEFS: Lower extremity functional scale
NRS: Numeric rating scale
NTR: The Netherlands National Trial Register
PRODISQ: PROductivity and DISease Questionnaire
PSFS: Patient specific function scale
RMDS: Roland Morris disability score
TTCM: Transmural trauma care model
VUmc: VU University Medical Center
